## Abstract

**Introduction:**

Recent years have witnessed an upsurge of demand in eye care services in the UK. With a large proportion of patients referred to Hospital Eye Services (HES) for diagnostics and disease management, the referral process results in unnecessary referrals from erroneous diagnoses and delays in access to appropriate treatment. A potential solution is a teleophthalmology digital referral pathway linking community optometry and HES.

**Methods and analysis:**

The HERMES study (Teleophthalmology-enabled and artificial intelligence-ready referral pathway for community optometry referrals of retinal disease: a cluster randomised superiority trial with a linked diagnostic accuracy study) is a cluster randomised clinical trial for evaluating the effectiveness of a teleophthalmology referral pathway between community optometry and HES for retinal diseases. Nested within HERMES is a diagnostic accuracy study, which assesses the accuracy of an artificial intelligence (AI) decision support system (DSS) for automated diagnosis and referral recommendation. A postimplementation, observational substudy, a within-trial economic evaluation and discrete choice experiment will assess the feasibility of implementation of both digital technologies within a real-life setting. Patients with a suspicion of retinal disease, undergoing eye examination and optical coherence tomography (OCT) scans, will be recruited across 24 optometry practices in the UK. Optometry practices will be randomised to standard care or teleophthalmology. The primary outcome is the proportion of false-positive referrals (unnecessary HES visits) in the current referral pathway compared with the teleophthalmology referral pathway. OCT scans will be interpreted by the AI DSS, which provides a diagnosis and referral decision and the primary outcome for the AI diagnostic study is diagnostic accuracy of the referral decision made by the Moorfields-DeepMind AI system. Secondary outcomes relate to inappropriate referral rate, cost-effectiveness analyses and human–computer interaction (HCI) analyses.

**Ethics and dissemination:**

Ethical approval was obtained from the London—Bromley Research Ethics Committee (REC 20/LO/1299). Findings will be reported through academic journals in ophthalmology, health services research and HCI.

**Trial registration number:**

ISRCTN18106677 (protocol V.1.1).

Strengths and limitations of this studyThe HERMES study (Teleophthalmology-enabled and artificial intelligence-ready referral pathway for community optometry referrals of retinal disease: a cluster randomised superiority trial with a linked diagnostic accuracy study) is a prospective, multicentre implementation science study assessing clinical utility, cost-effectiveness and human–computer interaction of Tele-Medicine and Artificial Intelligence Decision Support Systems in eye care referral pathways.The HERMES study incorporates three intertwined implementation science designs for digital eye care: an interventional, cluster randomised controlled trial of telemedicine, an observational postimplementation study of telemedicine and a prospective diagnostic accuracy study of artificial intelligence decision support systems.The study includes an embedded comprehensive economic evaluation, coupled with a human–computer Iiteraction analysis, generating evidence of enablers and barriers to real-life adoption of digital pathways.One limitation of the study is that the assessed care pathways pertain to the UK healthcare setting and may not be directly generalisable to other health systems, although reflecting a global trend towards digital transformation of healthcare.

## Background

Ophthalmology outpatient attendances account for 10% of all outpatient activities in the UK, more than any other individual medical specialty.^1 2^ Modern ophthalmic practice in the UK is faced by the challenges of an ageing population, increasing prevalence of degenerative disease and emergent treatments that are revolutionary but dependent on timely diagnosis. This represents a huge strain on diagnostic services and adversely impacts on timely access to care. Concurrently, there have been exponential increases in computing power and artificial intelligence (AI), expansions in the strength and ubiquity of communications technologies and developments in imaging capabilities, including in the community optometry setting.^3^

In the UK, primary care for ophthalmology is delivered by community-based optometry practices (high street opticians). A large proportion of patients diagnosed with a suspicion of retinal disease, including common conditions such as neovascular (‘wet’) age-related macular degeneration (AMD), are referred to Hospital Eye Services (HES) for diagnostics and disease management.^4 5^ The referral process results in unnecessary referrals (which can cause inconvenience and distress for patients), erroneous diagnoses, misclassification in terms of urgency, duplication of imaging tests and delays in access to treatment.

An increase in 30% in eye clinic attendances has been observed within the last 5 years throughout the UK.^6^ Further increases are likely because of the increasing availability of imaging technology, and especially optical coherence tomography (OCT), which is becoming ubiquitous in community optometry practices.^7^ OCT is a non-invasive imaging modality that uses light to generate micrometre-resolution three-dimensional images of the retina and provides the best way to diagnose a number of common retinal pathologies including wet AMD.

This study focuses on two potentially complementary digital technologies that have the potential to revolutionise the interface between community optometrists and hospital-based eye clinics: the teleophthalmology platform and the Moorfields-DeepMind AI DSS. The technologies will be assessed through two complementary and linked quantitative studies:

Cluster Superiority Randomised Trial (RCT) of teleophthalmology.Prospective diagnostic accuracy study of AI (machine learning) DSS (the Moorfields-DeepMind algorithm).

### Cluster superiority randomised trial (RCT) of teleophthalmology pathway

Telemedicine in ophthalmology can help face this challenge of provision of optimal and expert care to people attending for routine eye tests in community optometry practices, through a digital referral pathway relying on teleophthalmology links between community optometry and HES. This could optimise the referral process by allowing remote review of imaging and clinical data captured at the community level, by human experts based in HES. We will perform a cluster randomised superiority trial to assess the impact on service delivery metrics (such as proportion of unnecessary referrals and time from referral to treatment for urgent maculopathies) of a digital link between community optometry practices and HES using a teleophthalmology platform. We will use a device-agnostic, teleophthalmology platform to enable a digital referral pathway of patients with a suspicion of retinal disease. The pilot data produced by our research team have demonstrated the potential of teleophthalmology to drastically improve the efficiency of the referral pathway between community optometry and HES while reducing unnecessary referrals to HES^8^ and; hence, we propose a randomised trial powered to demonstrate superiority of the digital referral pathway against standard care.

### Diagnostic accuracy study of AI diagnosis support system

AI DSSs have recently been developed and shown to have good diagnostic accuracy against human experts in interpreting ocular imaging tests, such as OCT scan.^9^ The collaboration between Moorfields Eye Hospital and Google DeepMind produced the arguably most advanced deep learning DSS in ophthalmology, capable of interpreting OCT scans, providing diagnosis for retinal disease and suggesting urgency of referral. In silico analysis using retrospectively collected data has validated the tool against human experts for the diagnosis of retinal disease and referral recommendations, and it has been shown to be non-inferior.^9^ The algorithm is uniquely and independently used in Moorfields Eye Hospital for research purposes. Thus, while such work has demonstrated promising results, a prospective study is required to demonstrate its value in practice.

We will perform a prospective study to assess diagnostic (referral) accuracy of the Moorfields-DeepMind AI DSS when applied on the OCT scans collected in the context of the teleophthalmology RCT. This will allow maximum utilisation of collected data from the trial and will provide estimates and CIs of diagnostic (referral) accuracy. All cases included in the RCT will be reviewed by the Moorfields-DeepMind AI DSS within 48 hours of obtaining the OCT scans, and a referral decision (refer routinely, refer urgently, don’t refer) will be made by the algorithm for each case and recorded. The referral decisions made by the AI DSS will not be implemented in practice, yet data of the time required to obtain these decisions and any technical issues encountered with its use will be captured. These data will be incorporated into the implementation science models, including human–computer interaction (HCI) analysis, value-based economic evaluation and discrete choice experiment (DCE), to identify the potential opportunities and gaps in advancing the adoption of the Moorfields-DeepMind AI DSS.

### Impact of the COVID-19 pandemic: postimplementation observational pragmatic subtudy

National Health Service (NHS) services underwent rapid and significant adjustments across the board in response to extreme challenges presented by the COVID-19 pandemic. Changes to healthcare services driven by necessity are not always underpinned by a robust evidence base for efficiency and safety. In ophthalmology, as a response to the need for social distancing and minimising unnecessary hospital visits, teleophthalmology pathways were commissioned recently in some areas of England using digital link to facilitate referrals between community optometry and HESs. Greater Manchester was an early adopter of this approach and a majority of the optometry practices in that area are now referring to NHS eye units via a teleophthalmology link. This local change in standard care provides a unique opportunity to examine whether teleophthalmology works under usual conditions within the NHS. This substudy will allow us to record and measure variation in quality of healthcare within a local region to inform our inferences from the RCT on how the teleophthalmology pathway will perform within a real-life setting. We will, thus, perform a pragmatic, observational, postimplementation study involving community optometry practices in the Greater Manchester area. This will also serve as a safety analysis allowing us to identify potential safety signals of the teleophthalmology pathways and adding granularity to the economic and qualitative evaluations of the RCT.

#### Trial aims and objectives

There are two complementary aims (aims 1 and 2) pertaining to the linked quantitative studies assessing the two digital technologies (‘teleophthalmology’ and the ‘Moorfields-DeepMind’ AI). The qualitative research element (aim 3) using HCI methodology will run across both studies to provide evidence on implementation (table 1).

**Table 1 T1:** Aims and objectives of the HERMES study

Aims	Objectives
1. To assess the effectiveness and efficiency of a digital referral pathway between community optometry and Hospital Eye Services for referral of retinal disease enabled by a device-agnostic, tele-ophthalmology platform (superiority C-RCT).	Primary objective: To compare the proportion of referrals classified as unnecessary (cases that can be safely managed without a HES consultation) between current standard care and tele-ophthalmology digital referral pathway. Secondary objectives: To estimate the relative efficiency of the tele-ophthalmology digital pathway compared with standard care in both within trial-based evaluation. To compare the rate of inappropriate referrals (defined as wrong diagnosis or wrong level of urgency) between standard care and the tele-ophthalmology digital pathway. To capture the number of uncommon/complex retinal referrals to secondary care and the proportion that can be safely triaged through the tele-ophthalmology platform. To compare time from referral to review and/or treatment in HES for urgent referrals (such as Wet AMD and Retinal Vein Occlusions) between standard care and tele-ophthalmology digital pathway. To assess the number of false negatives (number of patients that would have benefited from a HES consultation but were deemed suitable for continued care in the community) (safety assessment)
2. To estimate the diagnostic (referral) accuracy and assess the ‘real-life’ performance of an Artificial Intelligence Decision Support System (the Moorfields-DeepMind AI) in the context of referral pathways between community optometry and HES.	To estimate the diagnostic (referral) accuracy of the Moorfields-DeepMind AI for recommending referral to HES from community optometry practices. To estimate the diagnostic accuracy of the Moorfields-DeepMind AI for the diagnosis of retinal disease. To assess the cost-effectiveness of the introduction of the DeepMind algorithm in the referral pathway between community optometry and HES. To assess the technical feasibility of using the Moorfields-DeepMind AI for real-time analysis of retinal OCT scan images. To assess real-time operational performance of the Moorfields-DeepMind AI in the tele-ophthalmology referral pathway.
3. To assess patient and healthcare professional acceptability as well as the barriers and enablers for the adoption of these digital technologies in the context of referral pathways between community optometry and HES through a human–computer interaction approach.	To understand current workflows and practices of staff and patients in community optometry and HES so as to identify key user requirements for tele-ophthalmology tools from the perspectives of both practitioners and patients (working with care settings with diverse established practices). To oversee the deployment of a digital referral platform at selected participating sites to ensure acceptability and acceptance by all user groups, and to understand the adoption process. To identify factors that shape professionals’ and patients’ attitudes to, and trust in, the Moorfields-DeepMind AI, and how to present information in ways that instil appropriate confidence. To observe workflows and practices of staff and patients in community optometry practices and HES with already established tele-ophthalmology pathways, aiding identification of technical, logistical and human factors affecting implementation of tele-ophthalmology in real-life (pragmatic sub-study).
4. To estimate the effectiveness and efficiency of a digital referral pathway between community optometry (High Street Opticians) and the Hospital Eyes Services for referral of retinal diseases enabled by a tele-ophthalmology platform in a real-life, observational post-implementation sub-study.	To compare the proportion of referrals classified as unnecessary (cases that can be safely managed without a HES consultation) against Reference Standard and the intervention arm of the RCT. To compare the rate of inappropriate referrals (defined as wrong diagnosis or wrong level of urgency) against the Reference Standard and the intervention arm of the RCT. To assess the number of false negatives (number of patients that would have benefitted from a HES consultation but were deemed suitable to continued care in the community) (Safety assessment). To compare time from referral to review and/or treatment in HES for urgent referrals (such as Wet AMD and Retinal Vein Occlusions) between post-implementation real-life tele-ophthalmology digital pathway and the intervention arm of the RCT. To estimate the relative efficiency of the real-life tele-ophthalmology digital pathway compared with the RCT tele-ophthalmology pathway.

AMD, Age-related Macular Degeneration; C-RCT, cluster randomised clinical trial; HERMES, Teleophthalmology-enabled and artificial intelligence-ready referral pathway for community optometry referrals of retinal disease: a cluster randomised superiority trial with a linked diagnostic accuracy study; HES, Hospital Eye Services; OCT, optical coherence tomography.

## Methods and analysis

### Study design

#### Superiority cluster randomised clinical trial of tele-ophthalmology pathway

An interventional superiority cluster randomised trial (RCT) will be performed comparing standard practice for referral of suspicious retinal disease with teleophthalmology between community optometry and HES. This part of the study will be reported according to the Consolidated Standards of Reporting Trials extension for cluster randomised clinical trial (C-RCTs).^10^

#### Diagnostic accuracy study of AI DSS

A prospective study will be conducted using the data of the above RCT to assess the diagnostic (referral) accuracy of an advanced AI DSS (the Moorfields-DeepMind Algorithm) for the automated diagnosis and referral recommendation for retinal disease. OCT scans transferred to the Moorfields Reading Centre in the course of the study will be assessed by the DeepMind algorithm in ‘real-time’ and its referral recommendations will be recorded and analysed for diagnostic (referral) accuracy and compared against the performance of human experts in the standard care and teleophthalmology arms of the RCT. This part of the study will be reported according to the STARD (Standards for Reporting Diagnostic accuracy studies) 2015 statement,^11^ or STARD-AI.^12^ A within-trial-based economic evaluation will estimate the efficiency of alternative referral models for retinal disease. A HCI analysis using qualitative methods will assess feasibility of implementation of both digital technologies.

#### Observational, postimplementations, pragmatic substudy

Community optometry practices in the Greater Manchester area will continue to refer patients with suspicious retinal disease to HES using the locally established teleophthalmology digital pathway. Referral recommendations will be compared against a reference standard provided by Moorfields Reading Centre to inform the assessment of real-life effectiveness and efficiency of the teleophthalmology referral pathway.

### Setting

For the C-RCT and diagnostic accuracy study, patients will be recruited at 24 optometry practices (clusters) in the catchment areas of four HES sites: Moorfields Eye Hospital NHS Foundation Trust (8–10 practices), Birmingham University Hospitals NHS Foundation Trust (4–6 practices), Central Middlesex Hospital at London North West University Healthcare NHS Trust (4–6 practices) and North West Anglia NHS Foundation Trust (4–6 practices). Twelve clusters (each cluster is an optometry practice) will be randomised to standard care and 12 clusters to the intervention (teleophthalmology). This selection of sites includes urban, suburban and rural locations within the UK allowing the inferences made from this study to be applicable to more of the UK population. Two additional optometry practices (clusters) will be randomised (1:1) in a reserve capacity in case of a cluster drop-out or in order to accelerate the recruitment process (online supplemental appendix 1)

10.1136/bmjopen-2021-055845.supp1Supplementary data

For the pragmatic, observational, postimplementation substudy, patients will be recruited at 12 optometry practices (clusters) in the catchment area of Manchester University NHS Foundation Trust. These practices have adopted a teleophthalmology referral pathway as standard practices.

The enrolment start date is September 2020 with anticipated primary completion date in August 2023. Eligible practices need to have OCT devices and the activity volume and track record of referral to HES that will allow achieving the per practice recruitment target.

All OCT scans and clinical vignettes from each case will be transferred to the Moorfields Reading Centre that will provide the reference standard (diagnosis and referral recommendation). All suitable OCT scans will be processed by the DeepMind algorithm at the Moorfields Reading Centre in ‘real-time’ for the AI diagnostic accuracy study.

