Secondary outcomes C-RCT: Proportion of wrong diagnosis and wrong referral urgency in standard and tele-ophthalmology pathways against the reference standard Proportion of false-negative referrals, as well as sensitivity and specificity in standard and tele-ophthalmology pathways against the reference standard Time from referral to consultation for urgent and routine referrals in standard and tele-ophthalmology pathways Time from referral to treatment for urgent maculopathies in standard and tele-ophthalmology pathways Number of uncommon referrals (rare disease) that can be safely triaged in the tele-ophthalmology pathway Within trial cost-effectiveness and cost-consequences of the tele-ophthalmology digital pathway compared with standard care Modelled cost-consequences and net benefits of alternative diagnostic and referral strategies	Secondary outcomes diagnostic accuracy study: Sensitivity and specificity of Moorfields-DeepMind AI for the diagnosis of retinal disease Sensitivity and specificity of Moorfields-DeepMind AI for referral urgency Proportion of false-positive referrals in the standard and tele-ophthalmology pathways when human assessors are replaced by the AI DSS Proportion of wrong diagnosis and wrong referral urgency in the standard and tele-ophthalmology pathways when human assessors are replaced by AI DSS Uptime and end-to-end inference speed of technical infrastructure supporting the AI DSS Average time of end-to-end output (referral recommendation) by the AI DSS Cost-consequences and net benefits of AI-enabled digital referral pathway	Secondary outcomes of pragmatic sub-study: Proportion of false-positive referrals in the tele-ophthalmology referral pathway against the Reference Standard and the intervention arm in the main RCT. Proportion of wrong diagnosis and wrong referral urgency in the tele-ophthalmology pathway compared against the Reference Standard and the intervention arm in the main RCT study Proportion of false-negative referrals compared against the Reference Standard and the intervention arm in the main RCT study Time from referral to review and/or treatment in HES for urgent referral) in the post-implementation real-life tele-ophthalmology digital pathway

AI DSS, artificial intelligence decision support system; C-RCT, cluster randomised clinical trial; HES, Hospital Eye Services.

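### The comparison of the Manchester sub-study with the RCT intervention arm cannot separate real-life setting from hospital, because no hospital is in both groups

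*Protocol article*

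**What the plan says.** The Setting section of the protocol article places the sub-study in one trust: "patients will be recruited at 12 optometry practices (clusters) in the catchment area of Manchester University NHS Foundation Trust". For the trial, "patients will be recruited at 24 optometry practices (clusters) in the catchment areas of four HES sites", and Manchester is not among the four. The same section defines a cluster as an optometry practice and allocates 12 clusters to each trial arm.

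Table 1 (Aim 4) plans to compare unnecessary and inappropriate referrals "against Reference Standard and the intervention arm of the RCT". It adds time to review or treatment for urgent referrals, compared with the intervention arm, and a further objective: "To estimate the relative efficiency of the real-life tele-ophthalmology digital pathway compared with the RCT tele-ophthalmology pathway". Table 2 lists, among the secondary outcomes of the sub-study, "Proportion of false-positive referrals in the tele-ophthalmology referral pathway against the Reference Standard and the intervention arm in the main RCT", with parallel entries for wrong diagnosis or urgency and for false negatives.

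The purpose is given in the section on the COVID-19 pandemic: "to inform our inferences from the RCT on how the teleophthalmology pathway will perform within a real-life setting". In the RCT intervention arm, clinicians at the corresponding hospital make the referral decision remotely. Randomisation is stratified by hospital site. The Statistical analysis section gives a model for the RCT primary outcome only and refers to an appendix that is not shown.

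**The concern.** In the intervention arm, a false-positive or false-negative referral is a decision by that hospital's reviewers, and time to consultation or treatment depends on that hospital's capacity. The trial itself stratifies on hospital. At that level the planned comparison has one unit on one side and four on the other, with none in common. Twelve Manchester practices look like twelve replicates of real-life teleophthalmology, but they share one receiving trust.

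An ordinary difference between hospitals could therefore be taken for an effect of routine implementation, or could mask one. This matters because the sub-study is also meant to serve as a safety analysis, and its economic part sets out to explain what drives any difference from the trial. The one limitation the article lists is transfer to health systems outside the UK, which does not cover this point.

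**Working it through.** **No stated figure to reproduce.** The article gives no sample size, event rate, intracluster correlation (ICC) or between-hospital variance for this comparison.

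**Step 1: can the two effects be separated?** From Setting:

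| Group | Practices | Hospitals |
|---|---|---|
| Sub-study | 12 | 1 (Manchester) |
| RCT intervention arm | 12 | 4 (none is Manchester) |

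In any regression, the indicator for real-life setting equals the indicator for Manchester. A setting effect and hospital fixed effects cannot both be estimated, whatever the unseen appendix contains.

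**Step 2: size on the odds-ratio scale.** Let τ be the between-hospital SD in log-odds (assumed). With unlimited patients, no true setting effect and equal weight for the four RCT hospitals, the variance of the difference is τ²(1 + 1/4). The 95% range of the odds ratio is exp(±1.96 × τ × √1.25).

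- τ = 0.3: 1.96 × 0.3 × 1.118 = 0.657, so 0.52 to 1.93.
- τ = 0.6: 1.96 × 0.6 × 1.118 = 1.315, so 0.27 to 3.72.

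Equal weights are slightly favourable to the plan. Setting gives 8–10 practices at one hospital and 4–6 at each of the others. A split of 9, 5, 5, 5 (assumed equal in proportion within the intervention arm) gives 1 + (9² + 3 × 5²)/24² = 1 + 156/576 = 1.27.

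**Step 3: what intervals clustered only by practice would miss.** This step is conditional, since the article does not say how intervals will be formed. For a difference in proportions with 12 practices per side and m patients per practice:

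- practice-level variance = p(1−p)[1 + (m−1)ICC] × 2/(12m)
- hospital variance = 1.27 σ², where σ is the between-hospital SD of the proportion
- true type I error of a nominal 5% test = 2[1 − Φ(1.96 × SE practice / SE total)]

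Take p = 0.2 and ICC = 0.05 (assumed) and m = 10 (the per-practice minimum stated for randomised practices, assumed for Manchester). Practice-level variance is 0.16 × 1.45 × 2/120 = 0.00387, so the SE is 6.2 points.

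| σ (assumed) | SE from hospitals alone | Total SE, m = 10 | Type I error, m = 10 | Type I error, m = 40 |
|---|---|---|---|---|
| 0 | 0 | 6.2 points | 5.0% | 5.0% |
| 3 points | 3.4 points | 7.1 points | 8.5% | 11.9% |
| 5 points | 5.6 points | 8.4 points | 14.6% | 22.6% |
| 10 points | 11.3 points | 12.9 points | 34.4% | 47.3% |

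The hospital term does not shrink with recruitment, so the understatement grows as m rises.

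**Step 4: can the four RCT hospitals serve as a yardstick?** If five hospital values are exchangeable, the chance that a given one is the highest or the lowest is 2/5 = 40%. Lying outside the range of the other four is therefore weak evidence. A 95% prediction interval from four values spans about ±3.18 × √1.25 = ±3.6 SDs, so it would rarely flag anything.

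**The case against.** The strongest reply is that the plan claims little here. The sub-study is called pragmatic and observational, Table 2 gives it secondary outcomes only, and the cost and consequence comparison is labelled exploratory. The design paragraph for the sub-study names only the comparison with the reading-centre reference standard, which a single-hospital sample does not confound. Local staffing, training and technical factors are also partly what the sub-study is meant to reveal, so hospital differences are not purely nuisance. This stands, and it limits the weight of the point. It does not remove it, because Aim 4 and Table 2 still name the RCT intervention arm as a comparator and the stated purpose is inference about real-life performance.

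A reader might infer that the plan will report intervals clustered by practice and so overstate its precision. The article does not say so: the only stated model is for the RCT primary outcome, and the cluster definition is the only hint. A reader might also infer that the investigators intend to attribute any difference to real-life implementation. No such causal claim is written, and the economic section leaves the drivers open.

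Finally, every between-hospital SD used here is an assumption. If hospitals do not differ, nothing is distorted.

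**Conclusion.** The point holds as one of complete confounding. The stated sites and the stated comparator make setting and hospital inseparable for outcomes decided at the hospital, and no later analysis can undo that. It assumes that the 12 practices refer to the trust in whose catchment they lie.

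The size is not known from the documents. The odds-ratio ranges of 0.52–1.93 and 0.27–3.72 rest on assumed SDs of 0.3 and 0.6, and the type I error figures rest further on a practice-clustered analysis that the article does not state.

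Only a secondary, observational comparison is affected. The RCT primary comparison, stratified by hospital, is untouched. Manchester's estimates against the common reference standard remain valid, as a description of one trust.

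**What to change.** Keep Manchester's estimates against the reference standard. Show them with confidence intervals beside the intervention-arm estimate of each of the four RCT hospitals, rather than only against the pooled arm. State that the comparison is descriptive.

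Do not use a position outside the range of the four hospitals as a test. If a prediction interval is shown, note that with four hospitals it is very wide. Individual hospital estimates will also be imprecise: half of 4–6 practices is 2–3, and at the 10-patient minimum that is 20–30 intervention-arm patients at each of three hospitals.

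Word conclusions as the Manchester pathway compared with the RCT hospitals, do not attribute differences to real-life implementation, and list the single-trust comparison among the limitations.

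The cost is one table and some wording, with no new data. The downside is a weaker claim from the sub-study.
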